## TREATMENT OF SUBJECTS

### 4.5 Investigational product/treatment

Each individual will consume one egg or egg product daily for a period of 90 days. These will be either modified or control eggs. The expiration time for eggs is 28 days. By using boiled eggs stored in a refrigerator this shelf life can be extended to 8 weeks.

The buttermilk product, which is pasteurized, tested for cooled shelf life for a period of 6 weeks, and 4 weeks at room temperature.

Testing shows the following concentrations for the eggs:

| In egg (mg/egg) | Lutein
Mg per egg yolk |          | Zeaxanthine
Mg per egg yolk |          |
|-----------------|---------------------------|----------|--------------------------------|----------|
|                 | mean                      | St dev   | mean                           | St dev   |
| Control         | 0,16778                   | 0,008655 | 0,08504                        | 0,001692 |
| Lutein          | 0,921422                  | 0,105767 | 0,137318                       | 0,013953 |
| Zeaxanthine     | 0,1743                    | 0,014454 | 0,487303                       | 0,031019 |

The omega-3 concentration is the same for all eggs and is  $200 \pm 10$ mg.

### 4.6 Use of co-intervention (if applicable)

Not applicable

### 4.7 Escape medication (if applicable)

Not applicable.

## 5. INVESTIGATIONAL MEDICINAL PRODUCT

Lutein, zeaxanthin and omega3 fatty acid are not medication but supplements. They are pro-vitamin and as such readily available at any drugstore. Furthermore, they are all naturally occurring supplements which are present in many vegetables (lutein and zeaxanthin) and fish (omega-3 fatty acid).

Testing shows the following concentrations for the eggs:

| In egg (mg/egg) | Lutein
Mg per egg yolk |          | Zeaxanthine
Mg per egg yolk |          |
|-----------------|---------------------------|----------|--------------------------------|----------|
|                 | mean                      | St dev   | mean                           | St dev   |
| Control         | 0,16778                   | 0,008655 | 0,08504                        | 0,001692 |
| Lutein          | 0,921422                  | 0,105767 | 0,137318                       | 0,013953 |
| Zeaxanthine     | 0,1743                    | 0,014454 | 0,487303                       | 0,031019 |

The omega-3 concentration is the same for all eggs and is  $200 \pm 10$ mg.

### 5.1 Name and description of investigational medicinal product

Not applicable

### 5.2 Summary of findings from non-clinical studies

Not applicable

### 5.3 Summary of findings from clinical studies

After 6 months of supplementation 10 mg (containing 5% of zeaxanthin) the serum level of lutein increased from 210 to 1000 nM/L and for zeaxanthin from 56 to 95 nM/L [60]. No toxicity was observed at 2.5, 5.0 or 10.0mg daily in persons over the age of 60 [16]. The potential antithrombotic effect of Omega-3 fatty acids may theoretically increase risk for bleeding, this theory has however no clinical support [15].

### 5.4 Summary of known and potential risks and benefits

To date there are no known risk or potential risk from the consumption of lutein [16, 17], zeaxanthin [16] or omega-3 fatty acid [15]. There have been gastrointestinal complaints been associated with omega-3 fatty acids intake but with no serious consequences [61]. Increased Cholesterol levels, induced by daily egg consumption has to date not been shown to be a significant factor for heart disease risk [62]. There is however evidence that lutein and zeaxanthin may protect against age-related macula degeneration [11, 42, 43, 45, 46, 58]. There is also sufficient data supporting the protective role of omega-3 on cardiovascular diseases [63] and it's independent association with lower levels of anti-inflammatory markers [64]. There is also indication of its beneficial effects on a myriad of other disorders [65].

### 5.5 Description and justification of route of administration and dosage

These supplements will be consumed in the form of an egg or egg product daily. Research have shown egg yolk as a effective and efficient vehicle for the absorption of lutein and zeaxanthin [12, 50].

### **5.6 Dosages, dosage modifications and method of administration**

Test subjects will receive one of four different products to consume during the trial period of 90 days. These will all contain 0.921422 mg/egg (st dev  $\pm$  0.105767) of Lutein, 0.487303 mg/egg (st dev.  $\pm$  0.031019) of Zeaxanthin, and 200 ( $\pm$  10) mg of Omega-3 fatty acids. The dosage is stated as approximately as there are either eggs or egg-products which are produced naturally and as so the concentration will vary from between eggs. The concentration in the egg product will be more uniformly as these are made from a single batch, which will give less variation in concentration than for those subjects consuming the egg itself. These products has to be taken daily for 90 days at lunch time as either an egg or a buttermilk drink containing one egg yolk.

### **5.7 Preparation and labeling of Investigational Medicinal Product**

The products supplied to the University of Maastricht for the human intervention study are from normal commercial production. They are produced in a HACCP certified poultry farms and an EU certificated egg processing facility. All appropriate food safety standards (Productschap Diervoederwetgeving en GMP-regeling) are rigorously applied to the ingredients, the processing and the packaging. As a HACCP poultry farm and an EU certificated egg processing facility, production records are retained and available for inspection as required under the EU legislation. We have produced some test batches for determining the shelf life time of the product. From the above, it goes without saying that these products are entirely suitable and safe for human consumption.

The modified eggs will be produced by Nelissen Pluimvee using feeds prepared by Research Diet Services B.V. in Wijk bij Duurstede. Coppelmans in Waalre will prepare the egg product.

The feeds for producing the enriched eggs will be formulated and produced within the legal requirements for animal feed. The use of lutein and zeaxanthin is regulated under EU regulation 1831/2003. The dosage of lutein and zeaxanthin in feed will not exceed the legal limit of 80 ppm in animal feed. For omega3 fatty acids is a component of some ingredients like linseed meal and fish oil. These products are not limited for use as feed ingredient. Nowadays these feeds are already in use to produce omega3 fatty acids enriched eggs.

Within the legal requirements no extra labelling of the investigational product is necessary. The normal expiry time for eggs is 28 days. By using boiled eggs stored in a refrigerator this shelf live can be extended to 8 weeks.

The buttermilk product is tested for shelf live for a period of 6 weeks.

### **5.8 Drug accountability**

The eggs will be produced by Nelissen Pluimvee. The boiled eggs will be prepared by Nelissen Pluimvee and distributed by the office of Newtricious. The eggs will be packed in board or plastic containers. The products will be transported to the Human Biology distribution facility where test subjects can collect their products.

#### **Influence of modified eggs on macular pigment**

---

The buttermilk drink will be prepared by Coppelmans and packed in 100 ml bottles. The products will be transported to the Human Biology distribution facility where test subjects can collect their products.

Returned products from test subjects will be returned to Newtricious, which will assure the destruction of the remaining products.

## 6. METHODS

### 6.1 Study parameters/endpoints

#### 6.1.1 Main study parameter/endpoint

Macular pigment optical density: the amount of measurable macular pigment in the macula region.

#### 6.1.2 Secondary study parameters/endpoints (if applicable)

Blood lutein, zeaxanthin, omega-3, and lipid levels. Change in visual acuity and contrast sensitivity.

#### 6.1.3 Other study parameters (if applicable)

Iris colour, diet, daily sun exposure time, alcohol consumption, anti cholesterol medication, vitamin supplement, and presence of intra ocular lens.

### 6.2 Randomisation, blinding and treatment allocation

Randomisatie zal middels loting plaatsvinden. Deze zullen een volgnummer krijgen welke zal bepalen in welke groep ze terecht komen. Er vindt geen blinding plaats.

Opmerking [TB2]: Randomization will take place by drawing lots. This will generate a tracking number, which will determine in which group a particular subject will fall. There will be no blinding.

### 6.3 Study procedures

#### Blood sampling

1. een lipiden profiel bestaande uit fasting totaal cholesterol, HDL cholesterol en Triacylglycerol. Hieruit kunnen we dan LDL cholesterol berekenen mbv de Friedewald formule.
2. apoA-I en apoB
3. een klinisch safety profile (ALAT, ASAT, creatinine, gamma GT, alkalisch phosphatase, bilirubine)
4. luteine en zeaxanthine
5. markers die een low grade inflammatory profile aangeven zoals hs-CRP
6. markers die endotheel functie weergeven zoals sICAM, sVCAM sE-selectin, en MCP-1
7. markers voor oxidatieve schade (zou moeten dalen door al die aox die je geeft) bv MDA en oxLDL
8. omega-3

We hebben hiervoor nodig per meetmoment:

1 serum buis 10 ml

1 EDTA buis 10 ml

## **Influence of modified eggs on macular pigment**

---

The researcher will take the blood using two vacuum viles using the appropriate needles. These will be stored after being processed in containers in an ultra low temperature freezer (minus 80° Celsius) situated at the Human Biology department.

### **Heterochromatic Flicker Photometry**

The non researched eye is blindfolded. Subjects take place on a chair and look through the ocular, with the eye being researched, at a white background where 3 black dots are depicted. They are initially instructed to look ad the centremost dot and to press the button on the remote as soon as it starts to flicker. They are told that the colour of the dots will change after the fifth time and that the test is not finished. A distinctive tone will alert them at the start of the second measurement. They are now instructed to look at and fixate on either the left or the right dot (depending on the measured eye). Subject are now meant to press again on the button of the remote as soon as they see the centremost dot flickering again, this in order to measure the peripheral field of vision. After these last five repetitions the same tone will indicate the end of the test.

### **SLO**

Test subject take place on a chair in front of the SLO and rest head on a chinrest with both temples again a cushioned stay. The test eye is aligned with the laser beam and the raster is focused on the retina. In the centre of the raster there appears a cross. Subjects are clearly asked to keep focusing on the cross which centres the raster onto the macula. All this can be followed on a monitor linked to the SLO. The researcher now takes a series of pictures of the macula using different colours. After about 3 minutes the test is completed. Subjects may come from behind the SLO. If they like they can see the pictures taken.

### **Reflectometer**

The patient will be seated with both forehead and chin supported. They will be instructed to look straight forward onto a bright white spot. The researcher will record the difference between the light entering and leaving the eye. The subject will not notice any of this. The difference will give us an adequate estimate of the amount of Macular Pigment.

### **Optical Coherence Tomography**

The patient will be seated with both forehead and chin supported on a rest. The OCT is aligned in front of the eye being tested. Subjects will be asked whether they see a green light, which they have to focus on. If that is not the case, an external fixation point, in the mode of a blinking LED, will be used. They will be warned that the apparatus will get quite close to the eye without actually touching it. We will point out that it is normal to see a moving light source during the test, this is the recording device. Clear instructions will be given as to when they may blink, this in order to obtain clear images. After about 4 minutes when the test is finished they can see the results if they like to.

### **Visual acuity test with the ETDRS-chart**

Subject will be seated at 5metre distance from the ETDRS-chart. This under optimal contrast sensitivity conditions (room dimly lid, and chart adequately lid by an other light source). Depending on the line and amount of mistakes subject made while reading the

chart with one eye closed at a time, their visual acuity will be drafted in a logarithmic-value.

#### **Contrast sensitivity**

Subjects will be seated with both chin and head supported by the chin and head rest looking straight ahead to a computer monitor at 2.25 meter away. One eye, the one not being tested, is blindfolded. The researcher will then instruct the subject to look at the monitor onto which a circle is displayed with clearly visible vertical stripes in black and white (and all the greyscale tones in between). These will alternate in a sinusal rhythm. The researcher can then change the contrast manually. Subjects are then instructed to say “yes” and “no” as to whether or not they see the stripes. In this manner the researcher will get ever closer to the threshold value for contrast sensitivity of the test subject. Once this value is reached the computer automatically changed to the next spatial frequency (subjects will be test on a total of 6 frequencies). Each time the researcher will adapt the contrast until the threshold is reached. This will continue for up to 10 minutes, depending on visual acuity and contrast sensitivity of subjects.

#### **Questionnaire**

This is a short list of question regarding personal information, iris colour, refractory correction, diet, and lifestyle. This will be in Dutch. Subjects will also be asked to keep a nutrition diary. A nutrition diary will be filled for three days during the trial.

#### **Informed consent**

Every subject participating in this trial will sign a standard form consenting to the trial and stating their understanding of the implication of their participation. This will be in Dutch.

### **6.4 Withdrawal of individual subjects**

Subjects can leave the study at any time for any reason if they wish to do so without any consequences. The investigator can decide to withdraw a subject from the study for urgent medical reasons. Data collected from subject will be destroyed immediately.

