### **6.6 Follow-up of subjects withdrawn from treatment**

As we are measuring change over time and as there is no adverse effect to be expected subject who withdraw will not be followed on. They will be encouraged to contact us in case of any doubt.

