### **6.7 Premature termination of the study**

If for any reason we are to believe that the eggs or egg products are having serious adverse effects on the test subject, the study will be immediately terminated, however unlikely such an event may be. Our measurements involves proven techniques which

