#### **Influence of modified eggs on macular pigment**

---

have already shown in many studies not to produce any SAE's, however, if such an event is to happen the study will also be terminated.

In either case test subjects will be informed in writing explaining the reasons for and possible action they need to take because of the serious adverse effects. All available measurement data will be destroyed, this in keeping with the subjects' anonymity.

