##### **7.3 Follow-up of adverse events**

All adverse events will be followed until they have abated, or until a stable situation has been reached. Depending on the event, follow up may require additional tests or medical procedures as indicated, and/or referral to the general physician or a medical specialist.

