### **10.4 End of study report**

The investigator will notify the accredited METC of the end of the study within a period of 8 weeks. The end of the study is defined as the last patient's last visit.

In case the study is ended prematurely, the investigator will notify the accredited METC, including the reasons for the premature termination.

Within 18 months after the end of the study, the investigator/sponsor will submit a final study report with the results of the study, including any publications/abstracts of the study, to the accredited METC. Data collected will be kept for 5 years after termination of the

study after which they will be destroyed. This in case samples have to be re-analyzed.

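### Sections 6.4 and 6.7 order the destruction of data after withdrawal and after a safety stop, against the protocol's own retention rules, and leave only completers to analyse

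*Protocol*

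**What the plan says.** Section 6.4 lets subjects leave at any time and adds that "The investigator can decide to withdraw a subject from the study for urgent medical reasons". The next sentence is "Data collected from subject will be destroyed immediately". It makes no exception for baseline, Day 45 or safety data, and it does not depend on a request from the subject.

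Section 6.6 says that "subject who withdraw will not be followed on". The reasons given are that the study measures change over time and that no adverse effect is expected.

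Section 6.7 says that if there is reason to believe that "the eggs or egg products are having serious adverse effects on the test subject, the study will be immediately terminated". Serious adverse events from the measuring techniques also end the study. In either case, "All available measurement data will be destroyed", for the sake of anonymity. The blood measurements listed in 6.3 include "een klinisch safety profile (ALAT, ASAT, creatinine, gamma GT, alkalisch phosphatase, bilirubine").

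Other sections point the other way:
- 7.2 has all reported or observed adverse events recorded, and serious ones sent to the ethics committee (METC).
- 7.3: "All adverse events will be followed until they have abated, or until a stable situation has been reached".
- 10.1 keeps data at least until the analysis and publication are finished.
- 10.4: "Data collected will be kept for 5 years after termination of the" study. The stated purpose is possible re-analysis of samples. It also has the METC told of an early end and the reasons.

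**The concern.** Destruction cannot be undone, and no later analysis plan can restore what it removes. Two things are at stake.

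The first is the primary comparison. The outcome is measured on Days 1, 45 and 90 (section 3) and analysed as repeated measurements (section 8). If the early readings of withdrawn subjects are erased, nobody can include them, compare them with completers at baseline, or test how far the result depends on who stayed. The trial is unblinded (6.2) and compares no eggs with a daily egg or buttermilk drink, so withdrawal could plausibly differ between groups.

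The second is safety. Destruction applies to subjects withdrawn for urgent medical reasons and to a study stopped for harm. These are the cases in which laboratory and eye measurements would help to tell an effect of the product from an effect of a procedure.

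**Working it through.** **1. The rules side by side**

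| Situation | Rule to destroy or stop | Rule to keep or continue | Can both be followed? |
|---|---|---|---|
| Data of a withdrawn subject | 6.4: destroy at once | 10.1: keep until publication; 10.4: keep 5 years | No, unless 6.4 is an unstated exception |
| Adverse event record of a withdrawn subject | 6.4: destroy at once | 7.2: record all events | Not on the plain reading of 6.4 |
| Measurements after a safety stop | 6.7: destroy all | 10.1 and 10.4: keep | No, unless 6.7 is an unstated exception |
| Follow-up of a subject who withdraws with an adverse event | 6.6: none | 7.3: until abated or stable | Only if 6.6 is confined to outcome visits, which it does not say |

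**2. How much is erased at the planned dropout**

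Inputs: 18 evaluable subjects per group and 10% dropout (4.4); five groups (Summary, study design); 100 subjects (4.1); three visits (section 3).

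- The plan's own figure: 18 / (1 − 0.10) = 20 per group, and 5 × 20 = 100. This reproduces.
- Withdrawals: 20 − 18 = 2 per group, and 5 × 2 = 10 of 100. Completers: 90.
- Scheduled subject-visits: 100 × 3 = 300.
- Assume that each withdrawal falls after Day 1 and before Day 90. Withdrawn subjects have then contributed between 10 × 1 = 10 visits (all leave before Day 45) and 10 × 2 = 20 visits (all leave after Day 45).
- With destruction, 90 × 3 = 270 visits remain. With retention, 280 to 290 remain.
- The other 10 to 20 visits never take place. They are lost through withdrawal and section 6.6, not through destruction.

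**3. Does the sample size change?**

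No. With a difference of 9%, SD 7%, alpha 0.017 (two-sided assumed) and 90% power, the normal approximation gives 2 × (7/9)² × (2.387 + 1.282)² = 16.3, rounded up to 17. The exact t calculation gives the stated 18. These 18 are the subjects left after the 10% loss. The English comment in 4.4 gives a different precision figure (11.7%), which is a separate matter.

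**4. What can still be analysed**

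Completers can be compared in the group to which they were randomised. Three things are no longer possible: a longitudinal analysis of everyone randomised, a baseline comparison of withdrawals with completers, and a missing-data sensitivity analysis based on observed data.

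**5. What survives a safety stop**

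Serious event reports (7.2) and the reasons for stopping (10.4) go to the METC. The laboratory safety profile and the eye measurements do not survive 6.7. Section 6.7 does not name adverse event records for destruction.

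**The case against.** **Exceptions to a general rule.** One can read 6.4 and 6.7 as specific exceptions to the retention rules, and 6.6 as ending outcome visits only. That is possible, but no section says so. It would resolve the wording, not the loss of data. For 6.6 and 7.3 it does reduce the conflict to a tension.

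**Narrow reading of 6.4.** The destruction sentence directly follows the one on investigator withdrawal and may cover only those cases. Fewer than 10 of 100 subjects might then be affected, but they would be the medically motivated withdrawals.

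**The named model.** The repeated-measures General Linear Model in section 8, in its usual form, drops subjects with a missing visit. Retention alone would therefore not bring withdrawn subjects into the analysis. This stands, and the fix has to address the model too.

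A reader might also infer more than the documents support:
- *A measured bias.* If completers gain 9% and withdrawals 0%, the mean of all randomised is (18 × 9 + 2 × 0) / 20 = 8.1%. With 4.5% in withdrawals it is (18 × 9 + 2 × 4.5) / 20 = 8.55%. The response of withdrawals is invented in both cases, and only one group is considered although the objective is a comparison. The gap also comes from missing Day 90 values, which retention would not supply.
- *All safety evidence is lost.* Section 6.7 concerns measurement data and safety-triggered stops only, and some information reaches the METC.
- *No analysis by randomised group is possible.* Completers can still be analysed that way.
- *A conflict with the annual report in 10.3.* Counts can be kept without individual measurements.

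**Conclusion.** The point holds in a limited form. The protocol explicitly orders destruction in 6.4 and 6.7. These rules conflict with retention in 10.1 and 10.4 and, for adverse event records of withdrawn subjects, with 7.2. Section 6.6 is in tension with 7.3.

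At the planned 10% dropout, with the plain reading of 6.4, about 2 of 20 subjects per group (10 of 100) lose all their collected data. That is 10 to 20 subject-visits per measure, if every withdrawal falls between Day 1 and Day 90. The analysis is then restricted to completers with no means of checking that restriction. The direction and size of any bias are unknown, and the planned sample size is unaffected.

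After a safety stop, all laboratory and eye measurements are lost, while serious event reports and the reasons for stopping remain with the METC.

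**What to change.** - **6.4:** keep coded data collected up to withdrawal unless the subject asks for deletion. Record the date of and reason for withdrawal.
- **Analysis (section 8):** include these data in the group randomised, with a repeated-measures model that accepts subjects with incomplete visits, such as a linear mixed model.
- **6.7:** replace destruction with coded retention for the 5 years of 10.4. Anonymity, the reason given for destruction, is already protected by the coding and restricted key in 10.1.
- **6.6 and 7.3:** reconcile the two for subjects who withdraw with an adverse event, so that staff have one rule.

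The cost is a change of protocol and consent wording. The consent form is not among the documents, so what subjects have been told about their data after withdrawal has to be checked. Retention should follow the wording that each subject signed.
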